## Abstract

**Background:**

Effectiveness of actions to reduce sugar-sweetened beverage (SB) consumption in children still needs to be improved. Furthermore, the growing concern about sustainable food systems encourages to develop sustainability-based interventions. The objective of this cluster randomised controlled trial is to evaluate the long-term effectiveness of nutrition- and environmental sustainability-based interventions on the reduction in SB intake and on the increase in tap water consumption in 3rd to 6th grade primary school children (8 to 11 years of age).

**Methods:**

Forty-eight French-speaking Belgian primary schools (equivalent to around 3500 pupils involved in the evaluation) are randomised using a factorial plan: (i) control, (ii) nutrition-based intervention, (iii) sustainability-based intervention, and (iv) both. The interventions (encouragement of water breaks; provision of posters, leaflets, reusable cups, and glass bottles; website; meetings at school) were undertaken from February 2022 to June 2023. Evaluation includes questionnaires for the children and their parents on various determinants of dietary behaviour, a 4-day diary to collect information on the child’s beverage consumption, and audits at schools. The first evaluation was conducted in Spring 2021 before any intervention, with the two post-intervention evaluations being held in 2022 and 2023. The main quantitative judgement criterion will be the change over time in the mean SB consumption (in ml/day) in the intervention groups compared with the control group. Given the context of the research (school), the safety of the intervention, and the content of data collection, a consent was acknowledged as unnecessary by the Ethical Committee of the Faculty of Psychology (ULB; n°073/2021), but children and parents are explicitly informed of their right to refuse to fill in the questionnaires.

**Discussion:**

Multicomponent interventions based on nutrition and on environmental sustainability, alone or mixed, will provide an original and topical insight into health promotion at school around dietary behaviours. The dissemination plan will enable to widely inform stakeholders, school staff, and families, in addition to the scientific community through the usual medium (articles, conferences), about the research findings in 2024–2025.

**Trial registration:**

ISRCTN Registry ISRCTN99843102. Retrospectively registered on 25 May 2021

## Introduction

### Background and rationale {6a}

For several decades, regular sugar-sweetened beverage consumption in children is one of the most common unhealthy dietary habits worldwide [1]. Its association with weight gain and obesity and the risk of dental caries has been clearly documented and underlined as particularly worrisome [1]. Despite declines in most high-income countries, levels of consumption remain too high overall [2]. Substitution to water consumption, and not to artificially sweetened beverages (also included in sweetened beverages (SB)), is a topical issue to decrease sugar-liking. Furthermore, overall hydration is often considered as insufficient [3]. The consequences of chronic inadequate water intake on health are much less clearly established [4, 5]. In particular, it may affect attention and cognitive performance in children [6]. Therefore, reducing SB consumption should go in pair with the increase in drinking plain water, especially since substitution is not systematic [7].

To reduce SB beverage consumption, especially among young people, some public health initiatives like taxes, advertising regulation, and reduced exposure in children’s usual places of living have been developed in some countries [8]. In addition, schools are potential settings where such an issue can be effectively addressed. Indeed, they are considered as relevant intervention places: they are supposed to be healthy environments, and health education is included in teaching [9]. However, SB are still available in some schools via vending machines or easily accessible around schools [10]. In addition, children may come to school with snacks including SB, due to their easy and pleasant use, but also in relation with a poor or restricted access to tap water at school [11]. Beyond the environment offered by the school, increasing awareness and involving parents at some point in such a behavioural change are crucial [12].

Several trials have been developed to improve beverage-related behaviour in primary school children [13–16]. They included various intervention contents (information, accessibility) and targets (children, parents, teachers—individually or together). Depending on the criteria of judgement, research has reported mixed findings [16]. Essentially, whereas decreased sugary-sweetened beverages and increased water consumption were reported most of the time [17–24], positive effects on body weight status were less likely [25, 26] although they have been shown in some trials [27, 28]. However, findings of most trials published so far have not been valued enough due to methodological reasons or unconvincing conclusions: short-term assessment, complex intervention package difficult to include in the daily life of school staff, uncontrolled or incorrectly randomised trials, particular populations, etc. [13, 15, 16]. Strikingly, this topic is subject to conflicts of interest which makes it difficult to disentangle study limits and the influence of private interests [29]. Thus, undertaking trials independently of funding from beverage producers is crucial.

More recently, a large body of evidence has been collected on the relationship between foods, dietary habits, and the environment [30]. Dietary habits, i.e. the food groups consumed, are particularly impactful on various environmental indicators [30, 31]. Along with the concern in the general population around the COVID-19 origins and climate change impact, demonstrations led by the young Europeans (e.g. the “Youth for Climate” initiative) encourage to evaluate whether new opportunities for health promotion can be addressed in this way. So far, very limited investigation has been made to appraise how environment-related messages would help modify behaviours [32, 33]. Indeed, substituting SB with tap water reduces the production, cost, and waste impact in addition to its benefits on health. Still, the effectiveness of basing interventions on such issues, along with the changes in the school environment (e.g. facilitating access to tap water), must be evaluated. From a conceptual point of view, the underlining cognitive process would differ from the one involved in nutrition-based arguments [34]. In this case, the expected benefits are collective, rather than individual as for health-related changes, and in the long term if ever measurable over a lifetime. Yet, the theory of planned behaviour (TPB) that may support the identification of potential mediating factors in nutrition and environmental behaviour change suggests a successful intervention basis [35, 36]. Also, emotional, oral and normative concerns related to the environment call for an extended conceptual framework of analysis [36].

In Belgium, SB consumption is particularly high in the general population including children [37], putting this country in the top five of the European countries with the highest prevalence of daily consumers [38]. After a decrease until the early 2000s, a plateau in daily consumption has been reported since [2]. In addition, social inequalities in SB consumption tend to increase in Belgian adolescents [39]. Furthermore, the overall water intake is considered insufficient in Belgium [40, 41] like elsewhere [42, 43].

Based on the SPIRIT checklist [44], this paper describes the protocol of the DRINK trial, for “Decreasing consumption of sugar-sweetened beverages and Raising tap water consumption through Interventions based on Nutrition and sustainability for Kids”, a cluster randomised controlled trial (cRCT) implemented in Belgian French-speaking schools. The originality of the DRINK trial lies in studying the potential interacting effectiveness of interventions with enablers in both nutrition and sustainability, by using a factorial plan of randomisation.

### Objectives {7}

The first objective of the DRINK trial is to evaluate the long-term effectiveness of nutrition- and sustainability-based interventions on the reduction in SB intake and on the increase in tap water consumption in 3rd to 6th grade children (8 to 11 years of age).

The secondary objectives are (i) to specifically study the potential interaction between nutrition- and sustainability-based information provided within the interventions, (ii) to identify individual and family moderators of the intervention effectiveness, (iii) to assess school staff adherence to the set of interventions and to identify obstacles in the implementation of the interventions, and (iv) to estimate the total cost of the interventions in order to plan their generalisation.

### Trial design {8}

DRINK is a cluster randomised trial carried out from 2021/2022 to 2023/2024, where clusters are French-speaking primary schools in Belgium. The randomisation follows a factorial plan leading to allocate schools into four balanced groups (Fig. 1): (1) nutrition-based interventions, (2) sustainability-based interventions, (3) both nutrition- and sustainability-based interventions, and (4) control schools.

**Fig. 1 Fig1:**
[figure not shown]
Factorial randomisation plan and planned analyses of the DRINK trial. Numbers correspond to the theoretical sample size needed (see the “Sample size {14}” section)

## Methods: participants, interventions, and outcomes

### Study setting {9}

The DRINK trial is conducted in the French-speaking schools of Belgium, which are geographically located in the Brussels-Capital Region and in Wallonia. Primary schools are organised in several networks (public and private), the education programmes being established by the Federation of Wallonia-Brussels (FWB).

### Eligibility criteria {10}

All schools under the aegis of the Ministry of Education (FWB) were eligible, the exception being those solely for children with disabilities or special needs. The design of the study requiring to follow students during two school years and for organisation reasons, schools not having students in 3rd to 6th grades, and those with less than 11 students by grade were excluded from the selection. Among the participating schools, all children schooled in the 3rd to 5th grades (8 to 10 years of age) at the initial evaluation were eligible unless they had important difficulties in reading and understanding French (such as some foreign children who have just arrived in Belgium).

### Who will take informed consent? {26a}

Given the context of the research (school), the intervention, and the content of data collection, a consent was not necessary. Instead, children and parents are informed of their right to refuse to complete the questionnaires. Refusal forms are kept at schools because all research data are kept pseudonymised to the research team.

### Additional consent provisions for collection and use of participant data and biological specimens {26b}

This trial does not involve collecting biological specimens for storage.

## Interventions

### Explanation for the choice of comparators {6b}

Since the randomisation follows a factorial plan, the comparators will include different control schools for each domain of intervention (Fig. 1). We will compare (1) groups #1 and #3 to groups #2 and #4 for assessing the effectiveness of nutrition-based actions, (2) groups #2 and #3 to groups #1 and #4 for sustainability-based actions, and (3) groups #3 and #4 to groups #1 and #2 for assessing any interaction between the two intervention types. Therefore, only schools allocated to group #4 will not benefit from the research intervention packages. However, the staff from these schools are encouraged to continue their ongoing projects about nutrition and sustainability, such situations being documented in the school questionnaires.

### Intervention description {11a}

The intervention package includes complementary actions aiming to promote various components potentially involved in health behaviours, namely the theory of planed behaviour [35, 36] (Fig. 2). Through the different actions, the interventions aim to include cognitive action (through documents and meetings), reinforce the community level (meetings), activate health behaviours (water breaks), and modify the school environment. Equity is addressed through the supply of bottles only to the children who need them. Such actions may act on attitudes, norms, and self-efficacy, these dimensions being documented in the questionnaires (see the “Plans for assessment and collection of outcomes {18a}” section).

**Fig. 2 Fig2:**
[figure not shown]
Intervention package and purposes of each component based on theory of planned behaviour (TPB) components. All documents are made available on a website, along with video capsules and interactive games for the children. Access to website is differentiated according to the group

The intervention package has been developed to be easily included in the daily life of schools, without important structural changes. Indeed, the school staff must deal with constraints in relation to the official educational programme changes and encouragement to include extra-curricular activities. Furthermore, the school staff are trained through various documents and regular phone contacts. In situ training has not been organised so that it can easily be generalisable to (all) the school authorities. To ensure long-term maintenance of the intervention, we purposely developed it in a way to be as adaptable as possible to various school situations.

In the three groups of intervention, some components are implemented towards either the school staff, children, or parents (Fig. 2 and Table 1). “Physical” actions (supply of bottles and reusable cups, water breaks, meetings) have been developed alongside information documents that disseminate general knowledge on the topics and practical suggestions (tips and answers to “frequently asked questions” adapted to each target (Table 1)). For instance, more information, such as scientific basis, is provided in teachers’ documents compared to the ones for the parents or children. Scientific basis has been carefully checked for, avoiding “preconceived ideas” without sufficient evidence.

**Table 1 Tab1:** Main messages included in the information documents according to the group of intervention

**Topics addressed**	**Nutrition**	**Sustainability**	**Mixed**
**Water**			
Place of water in daily life (thirst, sport)	C/P/T/Po	C/P	C/P/T/Po
“Simplicity” (accessibility) of drinking tap water (practical tips, including taste improvement and bottle washing)	C/P/T	C/P/T/Po	C/P/T/Po
Tap water vs. bottled water for health (minerals)	C/P/T/Po	T	C/P/T
Water origins and safety	C/P/T	C/P/T	C/P/T
Environmental harmful effect of bottled water (from extraction to home)		C/P/T/Po	C/P/T
Limitation of water wastage at home		C/P	P
**Sweetened beverages**			
Recommended frequency of SB consumption	C/P/T/Po	Po	C/P/T/Po
Health harms of sugar	P/T		P/T
Sugar content and acidity of manufactured SB	C/P/T/Po		C/P/T/Po
(Tap) water as a substitution for SB	C/T/Po	C/T/Po	C/T/Po
**Others**			
Tips for changing daily behaviour step by step	C/P/T	P/T	C/P/T
Recipes for healthy and sustainable beverages	P/T/S	P/T/S	P/T/S
Parents/teachers’ modelling and role	P/T	P/T	P/T
Marketing influences	C/P/T/Po	C/P/T	C/P/T/Po
Nutriscore use (tips for choice)	C/P/T	P	C/P/T
Toilet access at school	C/T	T	T
Waste associated with bottled beverages/use of bottle and reusable cups		C/P/T/Po	C/P/T/Po
Cost of bottled beverages	P/T	C/P/T	P/T
Beverages and global warming		C	C

All documents are given on paper and made available on a website, with the access being differentiated according to the group

*C* children leaflet, *P* parent leaflet, *T* pedagogical leaflet for teachers, *Po* posters, *S* summer booklet for children

The difference between the three groups is made by the content in the information provided, all schools (except group #4) being exposed to “water breaks” during the school day, bottles, or cups if they were asked for and meetings. Thus, group #3 receives mixed information related to both nutrition and health issues and sustainability issues. A similar graphic chart is applied to all documents, with specific colours for each group (blue for the nutrition group, green for the sustainability group, and light orange for the mixed group) to enhance the messages.

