### Outcomes {12}

The first quantitative judgement criterion will be the change over time in the mean SB consumption (in ml/day) in the intervention groups compared with the control group (Fig. 1). The secondary criteria of judgement will be the change in the proportion of children consuming SB each day on the one hand and in the mean consumption of water (in ml/day) on the other hand. Quantitative outcomes in ml/day will be evaluated through a 4-day booklet, while the daily consumption will be based on a short frequency questionnaire. These outcomes will be measured at the second wave of data collection and changes estimated by difference with the pre-intervention measurements. Findings at the first post-intervention data collection will also be presented once the trial is finished.

Among the secondary objectives of the DRINK trial, the same outcomes will be used to assess the potential interaction between nutrition- and sustainability-based interventions (Fig. 1). The other three secondary objectives will be assessed using complementary information as described below. Altogether, the information collected and the regular monitoring of the trial development (including cost which is one of the objectives) will also enable to develop a comprehensive process evaluation.

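### Components shared by all three intervention groups but not by control put half of their effect into each 2x2 margin and make the interaction contrast unable to measure interaction between the two kinds of message

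*Protocol article*

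**What the plan says.** The protocol article numbers the groups 1 (nutrition), 2 (sustainability), 3 (both) and 4 (control).

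Under Intervention description {11a}, in the text after Table 1, one sentence states both the single respect in which the active groups differ and what they have in common: "The difference between the three groups is made by the content in the information provided, all schools (except group #4) being exposed to" water breaks, bottles or cups on request, and meetings. Table 1 adds common messages. Water origins and safety, tap water as a substitute for sweetened beverages (SB), recipes, and adult modelling have identical entries in all three active columns.

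Explanation for the choice of comparators {6b} then fixes three factorial contrasts:
- nutrition: "groups #1 and #3 to groups #2 and #4 for assessing the effectiveness of nutrition-based actions";
- sustainability: "groups #2 and #3 to groups #1 and #4 for sustainability-based actions";
- interaction: "groups #3 and #4 to groups #1 and #2 for assessing any interaction between the two intervention types".

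Objectives {7} makes it a secondary objective to study "the potential interaction between nutrition- and sustainability-based information provided within the interventions". Outcomes {12} words the main criterion differently from {6b}, as the change over time "in the mean SB consumption (in ml/day) in the intervention groups compared with the control group".

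**The concern.** In a clean 2x2 design every component belongs to one factor or the other, and the cell with neither factor differs from the rest only by lacking both. Here the shared components belong to neither message factor. They are present in three cells and absent from the fourth.

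Each margin therefore compares schools that all have the shared components with schools of which half have them. The interaction contrast sets one exposed and one unexposed group against two exposed groups, so a working shared package looks like sub-additivity. Intervention description {11a} gives the shared components active roles (prompting the behaviour, changing the school environment), so a zero effect is not the protocol's own premise.

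At stake are the interpretation of the two main effects and the interaction question, which Background and rationale {6a} presents as the original feature of the trial.

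**Working it through.** **Inputs.** From Sample size {14}: control mean 200 ml/day, SD 120, 15% reduction (30 ml/day), alpha 5% (two-sided assumed), power 80%, intra-class correlation 0.08, 4 × 17 = 68 pupils per school, 12 schools per group. P is not given; the range 0 to −30 ml/day is assumed here.

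**The plan's own figure.** The individually randomised size is 252 per arm. Design effect = 1 + 67 × 0.08 = 6.36. Total = 2 × 252 × 6.36 = 3205 pupils, and 3205/68 = 47.1, hence 48 schools. This reproduces the stated 48 schools and about 3200 pupils. With 24 against 24 schools, SE = √(2 × 120² × 6.36 / (24 × 68)) = 10.59 ml/day, and power for 30 ml/day is 81%. The sample-size arithmetic is not at fault.

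**What the contrasts estimate.** Relative to group 4, with I for a true message interaction:
- group 1 = P + N
- group 2 = P + S
- group 3 = P + N + S + I
- group 4 = 0

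Then:
- nutrition margin = N + P/2 + I/2
- sustainability margin = S + P/2 + I/2
- interaction contrast = (I − P)/2, or I − P as a difference-in-differences

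Four groups give three differences, but there are four unknowns (P, N, S, I). I and P enter the interaction contrast only as I − P, so neither more schools nor covariates can separate them.

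**Size with I = 0.** The contrast is on the averaged scale of {6b}, SE 10.59:

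| P (ml/day) | interaction contrast | rejection at 5% |
|---|---|---|
| 0 | 0 | 5.0% |
| −10 | +5 | 7.6% |
| −20 | +10 | 15.7% |
| −30 | +15 | 29.4% |

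The difference-in-differences is twice as large, with an SE twice as large (21.2), so the test is the same.

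**Effect on the margins.** With groups 1 and 2 at 170 and group 4 at 200, a 30 ml/day margin needs group 3 at 140: (170 + 140)/2 − (170 + 200)/2 = −30. If part of the reduction is shared:
- half shared (P = N = S = −15; means 170, 170, 155, 200): margin −22.5, power about 57%;
- all shared (P = −30, N = S = 0; means 170, 170, 170, 200): margin −15, rejection about 29%.

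**Other contrasts from the same data.**
- Groups 1, 2 and 3 against 4 (36 against 12 schools): SE = √(120² × 6.36/68 × (1/36 + 1/12)) = 12.23, power 69% for 30 ml/day.
- Any single pair (12 against 12): SE 14.98, power 52% for 30 ml/day, detectable difference 42 ml/day at 80% power. Of these, 3 against 2, 3 against 1 and 1 against 2 are free of the shared components.

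**The case against.** The strongest reply is that the factors are whole packages, not messages. {6b} speaks of actions, intervention types and packages, and Outcomes {12} states the interaction as one between interventions. On that reading the margins are ordinary factorial main effects, and sub-additivity from a component delivered only once is genuine redundancy. This stands. It follows that the planned contrasts are not meaningless whenever P differs from zero. It does not rescue the objective in {7}, which names interaction between the two kinds of information.

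A reader might infer that the trial will report the messages as interfering with each other. The documents do not support that. P has no stated value, and even at −30 ml/day about 70% of trials would show no significant interaction. Setting a 30 ml/day difference-in-differences beside 15 ml/day margins would also mix two scales; on the scale of {6b} the figure is 15.

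Nor is the 29% in the all-shared case simply lost power. It is low power for a package-level effect, but an inflated false-positive rate if the margin is read as a message effect.

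Two further points stand. Bottles and cups were supplied on request and delivery was not fully standardised (Discussion), so P varies by school. And {12} already words the main criterion as intervention groups against control, so for that contrast the defect is disagreement with {6b} more than absence. Both {6b} and {12} refer to Fig. 1, which could not be read here.

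**Conclusion.** The point holds as a limit on interpretation. The {6b} margins estimate a message effect plus half of the shared effect. The interaction contrast is fully aliased with the shared components, so it cannot answer the message-interaction objective in {7}; it can be read only as package-level redundancy.

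For P between −10 and −30 ml/day the interaction estimate is shifted by +5 to +15 ml/day. The bias lies in the estimate; a significant false antagonism is the minority outcome (about 8% to 29% of trials). Margins fall to 22.5 or 15 ml/day if half or all of the planned 30 ml/day is shared.

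These figures rest on additive messages, the planning SD, intra-class correlation and school size, and an assumed P. The aliasing itself rests only on the protocol's description of what each group receives. Randomisation and the sample-size arithmetic are unaffected.

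**What to change.** Within one four-group multilevel model, of the kind already planned in {20a}:

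1. Reconcile {6b} with {12} and state which contrast carries the main criterion. Report groups 1, 2 and 3 together against 4, and each active group against 4, as effectiveness versus usual practice.
2. Label the {6b} margins as message plus half of the shared package.
3. Keep groups 3 and 4 against 1 and 2, but label it a package-level interaction aliased with the shared components, and do not interpret it as interference between messages. Reword the {7} objective to match.
4. Report 3 against 2, 3 against 1 and 1 against 2 as exploratory contrasts of message content, giving their limited power. State that group 3 is not the full sum of groups 1 and 2. In Table 1 the mixed column lacks, for example, the posters on minerals in tap water and on the environmental harm of bottled water, and the children's content on water wastage, cost and toilet access.

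The cost is wording and a few extra contrasts, with no new data. Trial status places the last data collection and the results still ahead, so the change can precede the analysis. The price is precision (SE 12.2 and 15.0 against 10.6 ml/day) and a more modest claim about message interaction.
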